### Aims and Hypotheses

The aims of this study are to (1) examine whether case management augmented by an mHealth device integrated into a youth mental health team can improve treatment outcomes for young people with a severe mental illness and (2) examine whether the mHealth device can predict mental deterioration versus health for those allocated to the integrated arm of the trial. We hypothesize that (1) case management for a severe mental illness enhanced by an mHealth device integrated into a youth mental health team will result in better outcomes than case management with an unintegrated device and (2) physiological data from an mHealth device will identify periods of mental deterioration.

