#### Integrated mHealth Device: unWIRED Intervention

Participants will receive case management for their mental illness as well as wearing the Embrace2 device. This device sends physiological measurements to the Empatica Research Portal, which can then be relayed to health service computers for the treating case manager to view. A dashboard generated by the program Splunk [25] provides case managers with information regarding each participant’s arousal, sleep, and activity from the previous day. Splunk captures, indexes, and correlates real-time data and generates graphs, reports, dashboards, and visualizations. The dashboard provides a visualization of the participant’s EDA and activity over a 24-hour period, as well as representing activity through *speed meters*, which present the participant’s level of activity. The program provides password-protected weblinks allowing clinical staff to view the dashboard from their clinical site. Each participant will also have access to activity-based information, which will be transmitted to their mobile phone’s Mate App. Based on the information provided, case managers and/or participants may choose to alter their management plan. For example, periods of high arousal and/or poor sleep may indicate a need for a medication change or a more assertive intervention. Continuous data will be visually inspected for significant deviations in physiological measures and the *speed meters* will be used to alert clinicians of significant change. Physiological information relayed to both the case manager and participant will be regularly reviewed and discussed during team meetings. Where possible, the use of the dashboard will be recorded in electronic medical records. Adherence to the device will be monitored through a portal that shows if the device is being worn and the data are streaming. If there are consecutive days of nonadherence, the research psychologist (SB) will contact the participant to find out the reason for the disconnection and attempt to troubleshoot. For example, the psychologist may ask participants to remember to wear or charge the device and insure it is paired with their phone.

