### Measurements

#### Overview

The primary outcome for the RCT is the extent to which the integrated mHealth device can prevent mental deterioration. The within-subjects components of the trial will examine if differences in activity, sleep, and EDA predict mental deterioration versus stability. A variety of measurements will be taken, including self-report, case manager report, biometric measures from the Embrace2, EMAs of stress, chart reviews, as well as qualitative reports from case managers and participants regarding the acceptability of the device. Multimedia Appendix 1 shows a summary of the measurements taken at each time point.

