#### Assessments of Mental Deterioration

Case managers and blinded clinical staff will make monthly assessments of participants using the Clinical Global Impression Scale (CGI) [26], the Social and Occupational Functioning Assessment Scale (SOFAS) [6], and chart reviews.

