##### The Clinical Global Impression Scale

The primary measures are consensus scores on the CGI severity and treatment response scales. Assessments are made by blinded clinicians, taking into account all relevant information to make ratings on two 7-point scales. The CGI is a brief, valid measure of symptom severity and treatment response, which has shown utility in measuring mental state as compared to similar scales [27,28].

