##### Chart Reviews

Clinical research staff will primarily conduct chart reviews using electronic medical records to make CGI and SOFAS assessments of participants in the trial. Charts will be examined for information including diagnosis, medication histories, and occasions of service (ie, treatment-as-usual information); the period between emergence of symptoms and intervention; evidence of illicit substance use; hospitalizations; indications of relapse; and evidence of case manager use of the portal.

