#### Trial Administration

Data will be collected from the Embrace2 in a continuous and ongoing manner for all participants. Case management and treatment will continue as per usual in the community mental health services. Case managers of participants in the integrated unWIRED arm will receive training on how to use the mHealth device and dashboard to monitor a participant’s mental state. Research staff will monitor the extent to which there are data uploaded from the device based on the Empatica Research Portal. If unWIRED participants are observed to have minimal adherence over consecutive days, the research psychologist can contact each participant to determine the reason for the disconnection and attempt to restore the device. During the trial, the research psychologist may send EMA text messages to the unWIRED participants to determine stress levels and their responses will be visible on the Empatica Research Portal. EMA messages will be sent according to a schedule and can also be sent manually by the research psychologist. Physiological data from each unWIRED participant’s previous day will be displayed on the Splunk dashboard, showing their activity, rest, and EDA. A link to the dashboard will be provided to case managers so they can view the information on their work computer. Case managers will use the information from the dashboard to enhance their clinical decisions. Clinical staff and participants will be encouraged to discuss data recorded from the device during their meetings and to include this information in their collaborative care plan. Case managers will be provided with a basic manual for interpreting the dashboard; however, a clinical response will be left to their clinical judgement. Throughout the trial administration, clinical staff will be asked to report on their participant’s ongoing functioning and distress, as described in the Assessments of Mental Deterioration section. The research team can provide support to case managers as needed.

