### Power Calculations and Statistical Analysis

The primary outcome for this study is to compare changes in treatment-related outcomes before and after the intervention for participants enrolled in the integrated versus unintegrated conditions. There are currently no trials examining the augmentation of treatment with an mHealth device, so sample size estimations are made using general calculations. Assuming a moderately sized advantage of the integrated (ie, unWIRED) versus unintegrated device on outcomes (effect size=0.5, 80% power, and a 2-tailed α of .05), we will require 63 participants per group.

The RCT component generally compares measures of mental health, distress, and functioning between the conditions, adjusted for baseline scores. For example, this analysis may focus on an intent to treat using a hierarchical linear model (HLM) to test the differential effects of the two treatment conditions, because this method allows the number of observations to vary between participants and handles missing data by calculating estimates of trajectories using maximum likelihood estimation. Fixed effects could be tested for intervention condition and time of assessment. Random effects in the unstructured models provide an index of the relative effects of the treatments over time. Fixed effects parameters may be tested with the Wald test (*t* test, *P*<.05, 2-sided) and 95% confidence intervals. Analyses will focus on the primary outcomes (ie, CGI scores) and secondary outcomes (eg, APQ6, BASIS-24, DASS-21, PSQI, and AQoL-8D) between the unWIRED group and the active control group, with the main outcome points being at the 6-month follow-up relative to baseline. All results are based on estimated mean values derived from HLM analyses. The within-subjects analysis will be comprised of linear fixed effects models using physiological measurements (ie, sleep, activity, and EDA) to predict measures of mental health, distress, and functioning. Baseline variables may be used as covariates when analyzing individual and between-group differences (eg, age, illness severity, treatments, and personality differences). Thematic analysis [38] will be used to examine individual and group qualitative feedback regarding the acceptability of the mHealth device and the unWIRED intervention for participants and case managers; there will be approximately 10-20 participants in the patient and clinician groups.

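### In Aim 2 the clinician-rated CGI and SOFAS can absorb the device data they are meant to be predicted by, so a positive result could not be read as device validity

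*Protocol article*

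**What the plan says.** Aims and Hypotheses limits the second aim to one arm: to "examine whether the mHealth device can predict mental deterioration versus health for those allocated to the integrated arm of the trial". Measurements, Overview names the predictors: "The within-subjects components of the trial will examine if differences in activity, sleep, and EDA predict mental deterioration versus stability". Power Calculations and Statistical Analysis gives the model as "linear fixed effects models using physiological measurements (ie, sleep, activity, and EDA) to predict measures of mental health, distress, and functioning".

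Assessments of Mental Deterioration says who rates: "Case managers and blinded clinical staff will make monthly assessments of participants using the Clinical Global Impression Scale (CGI", with SOFAS and chart reviews named in the same sentence. The CGI section adds that consensus scores are used and that "Assessments are made by blinded clinicians, taking into account all relevant information to make ratings on two 7-point scales". Chart Reviews says that research staff work mainly by "using electronic medical records to make CGI and SOFAS assessments of participants in the trial", and lists evidence of portal use among the things to look for.

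On what case managers in this arm know, the unWIRED Intervention section states: "Physiological information relayed to both the case manager and participant will be regularly reviewed and discussed during team meetings". It adds that use of the dashboard is entered in the medical record where possible. Trial Administration says that the dashboard shows activity, rest and EDA, that case managers are trained to monitor mental state with it, and that "Case managers will use the information from the dashboard to enhance their clinical decisions".

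**The concern.** A test of whether a signal identifies illness needs a criterion formed without that signal. Here the person who judges mental state has been trained to consult the signal. A case manager who sees raised EDA and little rest may score the participant as worse, or may chart a worse mental state that a research rater later reads. Part of the rating is then the predictor itself (incorporation bias).

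This is separate from the blinding of the randomised comparison. It arises among participants who all have the same allocation, so it remains even if no rater ever learns an allocation.

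At stake is one of the trial's two aims. Hypothesis 2 could be supported because clinicians believed the dashboard and not because physiology tracks illness, and a positive result could not tell the two apart. An analysis plan cannot take the device's influence out of ratings already made, so the matter must be settled before rating starts.

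**Working it through.** **Step 1. The plan's own figure.** The protocol gives no sample size or accuracy target for Aim 2. Its one calculation is for the randomised comparison: n per group = 2 × (1.960 + 0.842)² / 0.5² = 62.8, so 63. This reproduces the stated 63 and is not affected by this point.

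**Step 2. The passages side by side.**

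| Link | Where stated | Status |
|---|---|---|
| Aim 2 is within the integrated arm | Aims and Hypotheses; Methods, Overview | Stated |
| Predictors are sleep, activity, EDA | Measurements, Overview; Statistical Analysis | Stated |
| Case managers see activity, rest, EDA and use them to monitor mental state | Trial Administration | Stated |
| Route 1: case managers rate CGI and SOFAS | Assessments of Mental Deterioration | Stated |
| Route 2: research staff rate from the record | Chart Reviews | Stated |
| The record carries device-informed judgement | unWIRED Intervention; Chart Reviews | Inferred: these place dashboard or portal use in the record, not readings |
| Raters are kept from device information | None | Not stated; the Randomization section discusses blinding only as to allocation |

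Whether case managers contribute to the CGI consensus score is not stated. If they do, route 1 reaches the consensus CGI too.

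**Step 3. Direction before treatment response (illustrative).** Let rating = (1 − w) × clinical information + w × device signal, with both standardised. The assumptions are w = 0.1 to 0.3, reliability of clinical information 0.8, and true device-state correlation r. With c = √0.8 × r,

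correlation = [(1 − w)c + w] / √[(1 − w)² + w² + 2w(1 − w)c].

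For r = 0 and w = 0.1 this is 0.1 / √(0.81 + 0.01) = 0.11.

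| True r | w = 0 | w = 0.1 | w = 0.2 | w = 0.3 |
|---|---|---|---|---|
| 0 | 0.00 | 0.11 | 0.24 | 0.39 |
| 0.2 | 0.18 | 0.28 | 0.40 | 0.53 |
| 0.4 | 0.36 | 0.45 | 0.55 | 0.64 |

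**Step 4. Adding action on the signal.** The unWIRED Intervention section lets case managers and participants change management in response to the data. Suppose (assumed) that a signal in the top 20% leads to action that lowers severity by 0.3 or 0.6 SD, and that deterioration means the worst 20% of ratings. With r = 0.2 the AUC against the untreated true state is 0.60. From 400,000 simulated ratings, the AUC against the rating is:

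| Effect of action | w = 0 | w = 0.1 | w = 0.2 | w = 0.3 |
|---|---|---|---|---|
| None | 0.59 | 0.64 | 0.70 | 0.76 |
| 0.3 SD | 0.55 | 0.60 | 0.66 | 0.73 |
| 0.6 SD | 0.51 | 0.56 | 0.62 | 0.69 |

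Along every row incorporation raises the AUC; down every column action lowers it. The net result lies above or below 0.60 depending on two quantities that the document does not give.

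**Step 5. How far a false-positive rate depends on assumptions.** With r = 0, 63 participants × 6 monthly ratings = 378, and person means removed, the chance of a significant association at weights 0.1, 0.2 and 0.3 is:

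- device used in every rating, no missing data: about 50%, 99%, 100%;
- device used in half the ratings (device term zero in the rest): 17%, 59%, 96%;
- as the line above, with 30% of ratings missing and a 0.5 correlation between what the rater viewed and what is analysed: 7%, 13%, 31%.

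No one of these lines can be preferred from the document.

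**The case against.** **The net direction is not settled.** A reader might infer that device accuracy will be overstated. The documents do not support that: action on the signal is part of the intervention and can hide true prediction. In Step 4, a weight of 0.1 with a treatment effect of 0.3 to 0.6 SD gives 0.60 to 0.56, no higher than the true 0.60. This stands. It is a second distortion, however, and does not remedy the first.

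**Activity may be read both ways.** The Introduction links low activity to depression and high activity to mania. If raters score deviation in either direction, a linear model largely misses it; simulated false positives then stay near the nominal level (5% to 8%). The one-directional model fits EDA and rest better than activity. This stands.

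**Aim 2 has other evidence.** A reader might infer that all of Aim 2 rests on contaminated ratings. It does not. Chart-noted relapse and hospitalisation are collected, and integrated-arm participants report momentary stress themselves. But DASS-21 and BASIS-24 are taken only at baseline and 6 months and APQ6 adds only month 3, so the self-report scales cannot mark monthly periods of deterioration. CGI and SOFAS are the monthly clinical measures.

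**The chart route is partly inference.** A reader might also infer that device readings sit in the chart, or that case managers alone write it. The protocol says neither: it mentions records of dashboard use, where possible, and care by a multidisciplinary team. What stands is that the record may carry device-informed judgements and that nothing tells raters to set them aside.

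**The raters are called blinded, and the full protocol may say to what.** That is possible. But the article itself names unblinded case managers as raters and opens the CGI to all relevant information; allocation blinding does not answer a question within one arm.

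**Conclusion.** The concern holds for clinician-rated CGI and SOFAS in Aim 2. By the document's own text, integrated-arm case managers both use the predictors to judge mental state and rate the criterion, and research staff rate from records that may reflect those judgements. The effect on the device-rating association is upward before any treatment response. Its net direction and its size cannot be computed from the document. The correlations, AUCs and false-positive rates above rest on assumed weights, reliability, treatment effect and extent of device use; they show only that modest device weights can matter. The sample size and the randomised comparison are not affected by this point. The change should be made before rating begins, because as written a positive Aim 2 result on these scales could not be interpreted.

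**What to change.** Amend the assessment sections and the within-subjects paragraph of the analysis section as follows.

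1. Exclude integrated-arm case-manager CGI and SOFAS ratings from the Aim 2 criterion, including any contribution to a consensus score used for Aim 2. Keep them as descriptive data.
2. Instruct the blinded chart raters to score Aim 2 CGI and SOFAS from symptoms, mental-state findings and functioning reported or observed at contacts, disregarding dashboard, device and momentary-assessment entries. Have evidence of portal use extracted only after the rating is made.
3. Repeat the within-person analysis in the control arm and report it beside the integrated-arm result. Trial Administration has device data collected for all participants, and the Control Condition section says they are not returned to the case manager. Present hospitalisation as supporting evidence only: the protocol expects patients to be stable more often than deteriorating, so events may be few.

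The cost is a rater instruction, a fixed order of chart extraction, analysis wording and one further analysis. Case-manager ratings are lost for Aim 2. Control-arm wear is at the participant's discretion, so those data may be sparser, and momentary stress reports are requested only in the integrated arm. Device influence already absorbed into clinical notes cannot be fully removed and should be stated as a limitation.

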##### The Social and Occupational Functioning Assessment Scale

The SOFAS is an overall measure of social and occupational functioning used in psychiatric assessments. The SOFAS describes functioning of the participant at the time of the assessment. Its ratings are based on a 0-100 scale, reflecting excellent to grossly impaired functioning, with higher scores indicating better functioning.

##### Chart Reviews

Clinical research staff will primarily conduct chart reviews using electronic medical records to make CGI and SOFAS assessments of participants in the trial. Charts will be examined for information including diagnosis, medication histories, and occasions of service (ie, treatment-as-usual information); the period between emergence of symptoms and intervention; evidence of illicit substance use; hospitalizations; indications of relapse; and evidence of case manager use of the portal.

#### Participant Self-Report, With Time Point

##### Demographics

Demographic information includes gender, date of birth, and ethnicity and is collected at baseline only.

##### The 10-Item Big Five Inventory

The 10-item Big Five Inventory (BFI-10) [29] is a personality measure based on the 44-item Big Five Inventory [30]. The BFI-10 focuses on five broad personality domains, including openness, conscientiousness, neuroticism, extraversion, and agreeableness. It is rated on a 5-point Likert scale, ranging from 1 (strongly disagree) to 5 (strongly agree). The BFI-10 retained validity compared to the original version and its test-retest reliability was .75. This inventory is administered at baseline only.

##### The 21-Item Depression Anxiety and Stress Scale

The 21-item Depression Anxiety and Stress Scale (DASS-21) [31] is a measure of depression, anxiety, and stress over the previous week. Respondents rate each item on a 4-point Likert scale, ranging from 0 (not at all) to 3 (almost always). The DASS-21 has high reliability, a factor structure consistent with its subscales, and high convergent validity with other measures of anxiety and depression [32]. This scale is administered at baseline and 6 months.

##### The Behaviour and Symptom Identification Scale-24

The Behaviour and Symptom Identification Scale-24 (BASIS-24) [33] measures psychiatric symptoms and functional difficulties over the previous week. Items are rated from 0 (no difficulty/symptom never present) to 4 (extreme difficulty/symptom always present). It has adequate reliability (coefficient α from .75 to .91 for subscales), validity, and responsiveness to change (effect size for change=0.56). The scale is administered at baseline and 6 months.

##### Activity and Participation Questionnaire

The Activity and Participation Questionnaire (APQ6) [7] is a measure of the participant’s capacity to conduct their usual activities over the previous month. Consumer feedback and test-retest reliability indicates good construct validity. This questionnaire is administered at baseline, 3 months, and 6 months.

##### The Assessment of Quality of Life-8 Dimension

The Assessment of Quality of Life-8 Dimension (AQoL-8D) [34] is a health-related, multi-attribute, quality-of-life measure, which has 35 items measuring independent living, happiness, mental health, coping, relationships, self-worth, pain, and senses over the previous week. Results indicate it has strong validity, reliability, convergent validity, and predictive validity compared to other measures of quality of life. This measure is administered at baseline and 6 months.

##### The Pittsburgh Sleep Quality Index

The Pittsburgh Sleep Quality Index (PSQI) [35] is a 19-item self-report measure of sleep quality and disturbances over the previous 7 days. The PSQI was used to measure seven domains: subjective sleep quality, sleep latency, sleep duration, habitual sleep efficiency, sleep disturbances, use of sleep medications, and daytime dysfunction. The domains are rated from 0 (no difficulty) to 3 (severe difficulty). A PSQI score above 5 yielded a diagnostic sensitivity of 89.6% and specificity of 86.5% (κ=0.75, *P*<.001) in distinguishing between good and poor sleepers. Generally, good psychometric properties have been established for the PSQI, with acceptable internal homogeneity, test-retest reliability, and validity. This measure is administered at baseline and 6 months.

